## Abstract

**Background:**

Soft palate defects created during oral cancer surgery may prevent complete palatal closure and trigger palatopharyngeal insufficiency. One current treatment employs a rigid obturator prosthesis; an extension of acrylic resin at the level of the hard palate ensures surface contact with the remaining musculature. Unfortunately, airflow escape often causes hypernasality, compromises speech intelligibility, and creates swallowing problems (including leakage of food and fluid into the nasal airway). We plan to test a new removable denture featuring a thick dental dam that serves as a membrane obturator. The principal objective of the clinical trial is a comparison of speech handicap levels after 1 month in patients with acquired velar insufficiencies who wear either the new device or a conventional, rigid obturator. The secondary objectives are between-device comparisons of the swallowing handicaps and the health-related qualities of life.

**Methods:**

The VELOMEMBRANE trial is a superiority, open-labeled, two-way, random crossover clinical trial. Adult patients exhibiting velar or palatovelar substance loss after tumor excision and who are indicated for rigid obturator-mediated prosthetic rehabilitation will be recruited in two teaching hospitals in France. Fourteen participants will be randomly allocated to wear both prostheses for 1-month periods in either order. The new membrane obturator is a removable resin prosthesis incorporating a rigid extension that holds a dental dam to restore the soft palate. The primary outcome will be the extent of phonation-related disability (the overall score on the Voice Handicap Index [VHI]). The secondary outcomes will be the Deglutition Handicap Index and health-related quality of life scores of the European Organization for Research and Treatment of Cancer (EORTC).

**Discussion:**

High-quality evidence will be provided to document the utility of a new medical device that may greatly improve the management and quality of life of patients with acquired velar insufficiency.

**Trial registration:**

ClinicalTrials.govNCT04009811. Registered on 4 July 2019

**Supplementary Information:**

The online version contains supplementary material available at 10.1186/s13063-022-06163-6.

## Introduction

### Background and rationale {6a}

Acquired soft palate defects may be attributable to trauma, infection, or iatrogenic causes, but are usually caused by tumor excision or radiation necrosis. In 2018, the incidences of oropharyngeal cancer in France were 31.9 cases per 100,000 person-years for males and 10.9 cases per 100,000 person-years for females [1]. Soft palate tumors represent fewer than 15% of such cancers [2, 3]. Malignant soft palate tumors are commonly squamous cell carcinomas and are treated via chemoradiotherapy, radiotherapy, and/or surgery [4, 5]. Soft palate defects trigger velopharyngeal insufficiency associated with airflow escape, affecting swallowing (thus creating dysphagia) and speech (the vocal quality becomes hypernasal and intelligibility is compromised) [6–8]. These functional consequences impair the quality of life in both psychological and social terms.

The traditional approaches toward repair of soft palate defects include surgical reconstruction via flap placement and prosthetic rehabilitation with obturators, both combined with speech therapy [9]. Surgical reconstruction requires local, regional, or free flaps (depending on defect size) and affords definitive reconstruction [10, 11]. However, the limitations include a long hospital stay, possible donor-site morbidity, and risks associated with older age, systemic disease, radiotherapy, and/or the lack of adequate recipient vessels. A prosthetic pharyngeal obturator is a removable alternative allowing visual surveillance of cancer recurrence at low cost. The removable rigid prosthesis, designed in the nineteenth century, features a posterior extension that separates the oropharynx from the nasopharynx, efficiently restoring the sphincter when retention and stability are adequate [7]. A major limitation develops when the residual velopharyngeal muscles cannot contract to an extent permitting air passage modulation [8]. Such failure creates either a blockage or free space between the tissues and the obturator. Under such circumstances, the device does not fully restore phonation or swallowing function. The psychological and social repercussions compromise the quality of life. Optimal restoration of chewing and swallowing in such patients remains of great concern [12].

A recent case report described a membrane obturator prosthesis incorporating a dental dam that restored the soft palate, sealed the oropharynx during swallowing, and controlled nasal airflow during speech [13]. The rigid resin extension did not seal the opening, rather supporting a peripheral membrane that served as a valve that contacted residual tissue. Although the use of such a flexible obturator to treat soft palate defects seems promising, further clinical studies are required. We hypothesized that mimetic restoration of the velar anatomy using a membrane obturator (rather than a conventional rigid obturator) would be more likely to restore speech and swallowing functions and improve the quality of life of patients with acquired soft palate defects.

### Objectives {7}

Our principal objective in this random, crossover clinical trial is to compare the speech handicaps of patients with velar insufficiencies evident after surgery, and who were indicated for obturator treatment. The comparisons will be performed after patients wear either the new membrane obturator or a conventional rigid obturator for 1 month (in random order), employing the overall Voice Handicap Index (VHI) score. Our secondary objectives are to compare the swallowing status based on the global Deglutition Handicap Index (DHI) score and the health-related quality of life as revealed by answers to the questions posed by various domains of the EORTC QLQ-C30 and QLQ-H&N35 questionnaires.

### Trial design {8}

The trial protocol conforms with the Consolidated Standards of Reporting Trials (CONSORT) Statement. The trial design and protocol adhere to the Standard Protocol Items of the Recommendations for Interventional Trials (SPIRIT) criteria; the SPIRIT Checklist is attached (Table S1).

The VELOMEMBRANE trial is a superiority, open-labeled, two-way, random, crossover clinical trial comparing the new prosthesis to the rigid obturator in adult patients with acquired soft palate loss. The patients will wear both prostheses for 1-month periods in a random order.

## Methods: participants, interventions, and outcomes

### Study setting {9}

The bicentric trial will be conducted in the dental departments of teaching hospitals in Bordeaux (Prosthodontics and Periodontics Department, Saint André Hospital, Bordeaux, France) and Toulouse (Prosthodontics Department, Rangueil Hospital, Toulouse, France). Participants will be recruited from adults consulting the participating dental departments.

### Eligibility criteria {10}

The inclusion criteria will be:

- Age over 18 years

- Acquired loss of velar or palatovelar substance (class I and II a-d maxillectomies; Brown [2010]) after tumor excision

- Indicated for rigid obturator prosthesis rehabilitation

- Possible dental rehabilitation using a removable prosthesis (retention and stability assured without the use of glue, an extent of mouth-opening allowing finger entry, adequate saliva production, and a level of dexterity allowing of prosthesis insertion, removal, and cleaning)

- Provision of written informed consent

- Ability to speak and read French

- Availability and a willingness to present for regular follow-up during the entire study period

The exclusion criteria will be any of the following:

- Allergy to acrylic resin

- Current radiotherapy or chemotherapy

- Scheduled velar surgery during the 3 months required for prosthesis testing and analyses

- Prior maxillectomy (orbital floor or total)

- Pregnancy or lactation

- Participation in another interventional study

- An inability to give written informed consent

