### Intervention description {11a}

We will obtain alginate impressions of the dental arches. Each provisional dental prosthesis created on these casts will include a posterior metal wire embedded in the palatal plate to support the oropharyngeal obturator fabricated from Kerr impression compound and lined with “SS White” impression paste. The plaster model will be duplicated in silicone. Thus, the same impression will be used to produce both the reference and experimental obturators (palatal plates) employing standard resin-handling procedures. For the reference rigid obturator, a rigid extension of acrylic resin will be added at the level of the hard palate that will allow surface contact with the remaining musculature. In the new membrane obturators, the rigid resin extension will be positioned in the soft palate plane prior to removal from the mold. The borders will be trimmed to lie 5 mm distant from the (contracted) remaining musculature. Pins and grooves will be added to ensure membrane retention (Fig. 1). A thick dental dam (Dental Hygienic Corporation) will serve as the membrane and will be shaped to ensure a 10-mm overlap with the pharyngeal walls, effectively forming an artificial soft palate [13]. Each patient will wear each obturator for 1 month, in random order. A trial flowchart is shown in Fig. 2.

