**Fig. 1 Fig1:**
[figure not shown]
The membrane obturator prosthesis. **A** The device features a removable denture (or a palatal plate alone) with a rigid posterior extension (shown in the palatal and lateral views) and a thick dental dam. **B** The dental dam is inserted into the palatal groove and clipped onto medial denture pins. **C** Then the dam is pushed back, placed around the extension of the groove, and clipped onto exterior pins

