### Recruitment {15}

For achieving adequate participant enrolment to reach the target sample size, all new patients meeting eligibility criteria will be given the opportunity to participate in the study. A close coordination is made between the Dental departments and the Oncology and Maxilla-facial surgery departments of both teaching hospitals to identify and refer adequately potential participants.

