### Adverse event reporting and harms {22}

Adverse events that may occur will be monitored by the investigators and a research assistant. Possible adverse events include ingestion/inhalation of imprint materials, metal pins, resin, or prosthesis or membrane materials; oral injury; and allergies to acrylic resin, chrome-cobalt (of the metal pins), or latex.

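### The exclusion criteria cover one of the three material allergies the protocol foresees, so a patient with a known chrome-cobalt allergy (or latex allergy, if the dam is latex) is eligible as written

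*Protocol article*

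**What the plan says.** Eligibility criteria {10} of the protocol article gives seven exclusion criteria. One concerns allergy: "Allergy to acrylic resin".

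Adverse event reporting and harms {22} lists what may go wrong with the devices, including "allergies to acrylic resin, chrome-cobalt (of the metal pins), or latex".

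Intervention description {11a} says of the membrane obturator: "Pins and grooves will be added to ensure membrane retention", and "A thick dental dam (Dental Hygienic Corporation) will serve as the membrane". The caption of Fig. 1 shows how the parts meet: "The dental dam is inserted into the palatal groove and clipped onto medial denture pins". The rigid obturator is described in the same section without pins or dam.

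On exposure, Trial design {8} says "The patients will wear both prostheses for 1-month periods in a random order", and the abstract gives the number: "Fourteen participants will be randomly allocated to wear both prostheses for 1-month periods in either order".

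On entry, Recruitment {15} says "all new patients meeting eligibility criteria will be given the opportunity to participate in the study". Table 1 in Participant timeline {13} schedules eligibility screening before allocation and does not mention allergy.

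**The concern.** The acrylic entry shows that the authors regard a known allergy to a device material as a reason to keep a patient out. The harms section then names two more materials for which no such rule is given. One of them, chrome-cobalt, is tied there to the pins of the experimental device.

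In a parallel-group trial, some patients with such an allergy would be allocated the other device. In this crossover none would: whichever sequence is drawn, the patient is assigned the membrane obturator in one of the two periods.

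Patient safety is what is at stake. The plan foresees the reaction as an event to monitor, but does not require the simple history question that could prevent it in patients who already know of their allergy.

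**Working it through.** This is a comparison of sections; the arithmetic only gives scale.

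**Materials set side by side**

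| Allergen named in {22} | Component | Excluded in {10}? |
|---|---|---|
| Acrylic resin | Resin parts of both devices ({11a}) | Yes |
| Chrome-cobalt | Pins, stated in {22}; pins described only for the membrane device in {11a} | No |
| Latex | Not stated; the dam is the likely source | No |

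Allergens foreseen: 3. Excluded: 1. Not excluded: 3 − 1 = 2, of which one is documented in the device and one is inferred.

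**Does another criterion close the gap?**

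- The indication criterion refers to the rigid obturator, so it does not test suitability for the membrane device.
- The criterion on removable prostheses is spelled out as retention, stability, mouth opening, saliva and dexterity. It says nothing about materials.
- The other six exclusions do not concern allergy, metal or latex.
- Intervention description {11a} offers no latex-free or metal-free version.
- Criteria for discontinuing or modifying allocated interventions {11b} deals only with a participant who reports not using the device.

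**Scale, under an assumed prevalence**

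The planned number is 7 per sequence, so 2 × 7 = 14 (Sample size {14}). Let p be the proportion of otherwise eligible patients with a known allergy to either material. The documents do not give p; the values below are assumptions. They pool the documented and the inferred allergen, and suppose that neither investigator nor patient acts on the allergy.

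- Chance of at least one such patient: 1 − (1 − p)^14
- Expected number: 14p
- Otherwise eligible patients needed on average to enrol 14 once they are excluded: 14/(1 − p)

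| Assumed p | At least one of 14 | Expected number | Needed to enrol 14 |
|---|---|---|---|
| 0.5% | 6.8% | 0.07 | 14.07 |
| 1% | 13.1% | 0.14 | 14.14 |
| 2% | 24.6% | 0.28 | 14.29 |
| 5% | 51.2% | 0.70 | 14.74 |

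**The case against.** The strongest reply is that the two sections answer different questions. A harms list describes what may happen after exposure, including first reactions in patients with no known allergy, so it need not match the exclusion list. That is right, and the sections do not contradict each other. But acrylic resin appears in both, so this plan does not treat monitoring as a substitute for exclusion.

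Second, the article condenses protocol version 1.0, and a fuller list, screening form or information sheet might cover the point. This is possible and limits confidence. Still, the article does not skip the topic: it presents its list as the exclusion criteria and names one allergy of three.

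Third, a known allergy could surface anyway. Table 1 schedules a clinical examination and collection of information before allocation, at specialist departments. Patients are told about the experimental device, have time to reflect and may withdraw, and the prostheses are removable. All of this lowers the practical risk. None of it is a rule that both sites must follow.

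Fourth, latex is not tied to any component, so only the chrome-cobalt half is documented. This stands, and the latex half is conditional. Finally, the prevalence figures merely restate an assumed input. This also stands: the conclusion does not rest on them, and the 51.2% should carry no weight of its own.

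**Conclusion.** The point holds. The exclusion list is incomplete against the plan's own list of hazards: of three foreseen material allergies, one is excluded and two are not. For chrome-cobalt this follows directly from the text. For latex it rests on the inference that the dam is the source, a reasonable one because the dam is the only membrane material described. Confidence is medium, because the full protocol may say more. The size that can be stated firmly is the count; the probabilities are illustrations. The matter concerns safety at entry and leaves the treatment comparison untouched. It should be corrected because the hazard is already recognised and the remedy is simple.

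**What to change.** Replace the single-material criterion in Eligibility criteria {10} with one excluding known allergy to acrylic resin, chrome-cobalt or latex. Ask about all three at the eligibility screening in Table 1, which comes before the obturators are fitted.

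The cost is one line of text and one history question. If the change counts as an important amendment, it also needs the ethics committee's favourable opinion and the ANSM authorization described in the section on protocol amendments {25}. Over the assumed range, 14.1 to 14.7 otherwise eligible patients would be needed on average to enrol 14, fewer than one extra. Trial status reports that recruitment started in July 2020, with an initial deadline of April 2022 that may be extended, so the change protects only patients not yet enrolled.

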### Who will take informed consent? {26a}

All participants will be told of, and given an information sheet including, the names and affiliations of the investigators, a plain-language description of the study (the reference and experimental interventions), study duration, their right to withdraw at any time without giving reasons, ethics committee approvals, and the personal data privacy guarantee. After a period of reflection, during the enrolment visit, the written informed consent will be taken by the investigators.

### Additional consent provisions for collection and use of participant data and biological specimens {26b}

N/A. Neither collection nor use of participant data and biological specimens.

## Interventions

### Explanation for the choice of comparators {6b}

The conventional device, a rigid obturator (reference), rarely fully satisfying in restoring oral functions, will be compared to a new device, a membrane obturator, mimicking the missing anatomical structures.

### Intervention description {11a}

We will obtain alginate impressions of the dental arches. Each provisional dental prosthesis created on these casts will include a posterior metal wire embedded in the palatal plate to support the oropharyngeal obturator fabricated from Kerr impression compound and lined with “SS White” impression paste. The plaster model will be duplicated in silicone. Thus, the same impression will be used to produce both the reference and experimental obturators (palatal plates) employing standard resin-handling procedures. For the reference rigid obturator, a rigid extension of acrylic resin will be added at the level of the hard palate that will allow surface contact with the remaining musculature. In the new membrane obturators, the rigid resin extension will be positioned in the soft palate plane prior to removal from the mold. The borders will be trimmed to lie 5 mm distant from the (contracted) remaining musculature. Pins and grooves will be added to ensure membrane retention (Fig. 1). A thick dental dam (Dental Hygienic Corporation) will serve as the membrane and will be shaped to ensure a 10-mm overlap with the pharyngeal walls, effectively forming an artificial soft palate [13]. Each patient will wear each obturator for 1 month, in random order. A trial flowchart is shown in Fig. 2.

**Fig. 1 Fig1:**
[figure not shown]
The membrane obturator prosthesis. **A** The device features a removable denture (or a palatal plate alone) with a rigid posterior extension (shown in the palatal and lateral views) and a thick dental dam. **B** The dental dam is inserted into the palatal groove and clipped onto medial denture pins. **C** Then the dam is pushed back, placed around the extension of the groove, and clipped onto exterior pins

**Fig. 2 Fig2:**
[figure not shown]
VELOMEMBRANE flowchart. The trial will evaluate the speech handicap in patients with acquired velar insufficiency at 1 month after wearing either the experimental membrane obturator or a conventional rigid obturator, based on the overall Voice Handicap Index (VHI) score, at the Bordeaux and Toulouse University Hospitals

### Criteria for discontinuing or modifying allocated interventions {11b}

If a participant declares not using the study obturator, he/she will be considered as a drop-out at the time of the study visit.

### Strategies to improve adherence to interventions {11c}

During the study, participants will have only the obturator to be used in the month in question. At each study visit, they will be asked if and how they use the obturator.

### Relevant concomitant care permitted or prohibited during the trial {11d}

Chemotherapy, radiotherapy, and maxillofacial surgery are prohibited during the trial as these treatments can affect the oral functions (oral pain, intolerance to prosthesis, loss of prosthetic adaptation, etc.).

### Provisions for post-trial care {30}

At the end of the study, patients will be proposed to continue their long-term oral follow-up at the Dental department of the Bordeaux or Toulouse teaching hospital.

### Outcomes {12}

The primary outcome will be phonation-related disability based on the overall score of the Voice Handicap Index (VHI) [14, 15] at 1 month after delivery of either prosthesis. This ranges from 0 and 120; the VHI includes 30 items exploring functional, emotional, and physical domains. The secondary outcomes include the Deglutition Handicap Index (DHI, 30 items, maximum score 120) and the EORTC QLQ-C30 (a general questionnaire containing the QLQ-H&N35 modules [35 items in all] exploring the health-related quality of life) prepared by the European Organization for Research and Treatment of Cancer (EORTC) [16–18]. Both questionnaires are scored from 0 to 100 and will be evaluated at 1 month after the delivery of either prosthesis. All questionnaires have been translated into French and validated.

### Participant timeline {13}

The study timeline is summarized in Table 1. Patients will be included over 21 months, and the trial will run for 3 months, creating a final duration of study of 24 months.

**Table 1 Tab1:** VELOMEMBRANE study timeline: enrollment, interventions, and assessments

		Study time			
		Enrolment and allocation	Post-allocation		Close-out
Timepoints	−t_1_	0	M1 30 days	M2 60 days	M3 90 days
Enrollment					
Clinical examination	✓				
Collection of dental arch Impressions	✓				
Occlusion examinations	✓				
Eligibility screening	✓				
Collection of information	✓				
Obtaining informed consent		✓			
Allocation to groups		✓			
Collection of velopharyngeal impressions		✓			
Interventions					
Fitting of obturator prostheses			✓	✓	
Assessments					
Questionnaire surveys			✓	✓	✓

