### Sample size {14}

Sample size calculation is based on the average comparison of crossover tests: the *t*-test for difference of means in 2 × 2 crossover design (N-Query software). We assume that the use of the rigid obturator will be associated with a mean VHI score of 34 and a standard deviation of 15 [14, 15]. To ensure a power of 90%, an alpha risk of 5%, and an expected difference of 15 points between the reference and new obturator, 7 patients per treatment sequence are required, thus 14 in all. No drop-out was included in the sample size calculation due to the small duration of the study follow-up (3 months).

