## Assignment of interventions: blinding

### Who will be blinded {17a}

N/A. Neither investigator nor patient will be blinded.

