## Data collection and management

### Plans for assessment and collection of outcomes {18a}

The VHI questionnaire will be administered by the investigator at baseline and 1 month after the delivery of either prosthesis. The secondary outcomes will be obtained from self-administered questionnaires completed at baseline and 1 month after each device is tested. Patient’s answers will be entered in e-CRF through a dedicated REDCap entry mask.

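### Allocation takes place 30 days before the first device is fitted, so a patient lost in that month stays in the primary analysis without informing it; allocating at the first fitting would be a cheap improvement.

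*Protocol article*

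**What the plan says.** In the protocol article, Table 1 (Participant timeline {13}) has these rows:

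- "Allocation to groups": ticked at time 0, together with consent and the velopharyngeal impressions.
- "Fitting of obturator prostheses": ticked at M1 (30 days) and M2 (60 days).
- "Questionnaire surveys": ticked at M1, M2 and M3 (90 days), and at no earlier visit.

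M1 and M2 stand under the post-allocation heading. The two one-month wearing periods are therefore M1 to M2 and M2 to M3, and the first 30 days after randomisation pass without a trial device.

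The section on non-adherence and missing data {20c} specifies intention-to-treat with a missing=failure rule and states no exception for patients who were never fitted. It adds sensitivity analyses by multiple imputation, available data and maximum bias. Sample size {14} gives 7 patients per sequence and says: "No drop-out was included in the sample size calculation". Intervention description {11a} says that "the same impression will be used to produce both the reference and experimental obturators".

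**The concern.** Only the order of the devices is randomised, and that order is first needed when the first device is handed over. Allocating a month earlier puts patients into the analysis set during a period in which they can be lost without trying either device. The patients have had cancer surgery, and the section on concomitant care {11d} prohibits chemotherapy, radiotherapy and maxillofacial surgery during the trial, so a change in cancer care is one plausible route to loss. Withdrawal or a failure in making the devices are others.

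Such a patient has both primary scores missing. With 14 patients and no allowance for drop-out, one or two such losses matter for power. Under the stated missing-data rule they may also pull the estimated difference towards zero.

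**Working it through.** **Inputs from the article.** Allocation at day 0 and first fitting at day 30 (Table 1). Expected difference 15 points, standard deviation 15, power 90%, alpha 5%, 7 per sequence, 14 in all (Sample size {14}).

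**Assumptions.** The article does not say whether 15 is the standard deviation of a single score or of the within-patient difference, nor whether the test is two-sided. I take SD_diff = 15, which equals a single-score SD of 15 with within-patient correlation 0.5, and a two-sided test. The number of losses is also assumed.

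**Step 1: the time without a device.** 30 − 0 = 30 days, one third of the 90 days from allocation to M3.

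**Step 2: the plan's own sample size.** Power comes from the noncentral t distribution with N − 2 degrees of freedom and noncentrality 15 × √N / SD_diff, which equals √N here.

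- N = 14: noncentrality √14 = 3.74, power 0.929.
- N = 12: noncentrality √12 = 3.46, power 0.876.

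Seven per sequence is thus the smallest balanced size that reaches 90%, and the stated 14 is reproduced.

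**Step 3: losses before fitting.** Two readings are possible, and they are alternatives.

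- *Scored as failure in both periods with the same value.* The patient contributes a difference of zero. With k losses the expected estimate is 15 × (14 − k)/14, and the sequences stay at 7 and 7.
- *Excluded.* The expected estimate stays at 15, but N falls to 14 − k.

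Power was simulated with 200,000 runs of the sequence-adjusted t-test:

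| Losses | Expected estimate, scored | Power, scored | Expected estimate, excluded | Power, excluded |
|---|---|---|---|---|
| 0 | 15 | 0.929 | 15 | 0.929 |
| 1 | 15 × 13/14 = 13.9 | 0.906 | 15 | 0.905 |
| 2 | 15 × 12/14 = 12.9 | 0.875 | 15 | 0.877 |
| 3 | 15 × 11/14 = 11.8 | 0.834 | 15 | 0.836 |

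The two readings differ in the estimate but hardly in power. Power falls below the planned 90% from the second loss.

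**Step 4: dependence on the SD.** If 15 is the SD of a single score, power at N = 14 before any loss is 0.68 with correlation 0, 0.83 with 0.3 and 0.97 with 0.6. The levels in the table therefore hold only for SD_diff = 15.

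**The case against.** The strongest reply is that the damage comes from the missing=failure rule and the absent drop-out allowance, not from the date of allocation. Correcting those two would deal with losses before fitting and also with losses after M1, which a later allocation does not touch. The planned available-data and multiple-imputation analyses would also show the result without failure scoring. This is fair and limits the weight of the point. It does not remove it, because those analyses are secondary to the stated primary rule and cannot restore a lost pair.

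A second reply is that early allocation may help the workshop: Table 1 fits one device at M1 and the other at M2, so a centre that knows the order can finish the first-period device first. One shared impression does not mean that both devices are finished by M1. This stands, and is the real price of the change.

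Third, the full protocol is not shown and may contain a replacement rule. It may, but replacing a randomised patient would still leave the lost patient in the intention-to-treat set under the rule as stated.

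A reader might also infer that the primary result is biased because baseline is measured after an open allocation. Outcome collection {18a} states: "The VHI questionnaire will be administered by the investigator at baseline and 1 month after the delivery of either prosthesis", and on blinding {17a}: "Neither investigator nor patient will be blinded". The first questionnaires are at M1, so baseline does follow allocation. But the primary outcome is the score one month after each device, and the model in the statistical methods {20a} has no baseline term. Nor does the article say that the patient learns the order at time 0. The documents support an effect on the description of baseline only, not on the device comparison.

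**Conclusion.** The point holds as an efficiency improvement. The 30-day gap and the rule that keeps every randomised patient in the analysis are explicit in the article. The size is modest: one loss leaves power at about 0.91, still above the target, and two bring it to 0.88. The dilution of 1/14 per loss rests on failure meaning the same score in both periods, and the power figures rest on SD_diff = 15 and a two-sided test. No loss rate is given, so the expected number of losses cannot be stated.

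Two stronger conclusions should not be drawn. A loss does not both shrink the estimate and remove a pair with unbalanced sequences: if it is scored, the sequences stay at 7 and 7; if it is excluded, the estimate is not shrunk. And under the equal-score assumption the pull is towards no difference, so this feature does not favour a false finding of superiority.

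**What to change.** In Table 1, move the "Allocation to groups" row from time 0 to the M1 visit, after the baseline questionnaires and immediately before the first fitting. Keep consent and impressions at time 0. Change the order of the e-CRF steps to match. A patient lost before fitting is then never randomised and can be replaced, so the analysis set remains 14 patients who reached the first fitting. Losses after M1 are unaffected and still depend on the missing-data rule.

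Costs: both devices must be ready by M1, because either may be the first. Recruitment began in July 2020 (Trial status), so the change needs an amendment. If it counts as important under the section on amendments {25}, it requires a favourable ethics committee opinion and authorisation from the national agency before use. It applies only to patients not yet randomised, so the report should say which patients were allocated under which timing.

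A minor side benefit is that the baseline questionnaires would precede allocation.
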